## Procedures for data review and editing

After randomisation each patient will be given a unique study number. The site investigator or designee will handle an enrolment log (*Subject ID log* and *Screening log*, appendix 29.7 and 29.8) which include the patients name, date of birth and study number. Subsequent data will be identified only by the study number. No identifiable data will be entered to the CRF. The enrolment log will be stored separately at each study site.

Data that are not uploaded to the CRF will be handled by the site investigator only. The SI is responsible for an interview of the involved personnel, to gather the necessary data and to edit and upload this to the secure database and entry into the CRF. The data file from the monitor used in all randomised patients, and the ultrasound images from the patients in the intervention group, are preserved and protected in the REBOARREST data space in HUNT Cloud. Data integrity policies and data integrity controls are to ensure that investigators cannot remove raw data, and that duplicate copies can be made available for accountability audits.

If an investigator for some reason must withdraw from the study, his/her responsibility is transferred from this investigator to the site investigator and the project management, which will make efforts to appoint a new investigator, if necessary.

## Specified retention period

Electronic database and study archive are maintained for at least five years. Individual patient data records will be handled according to the legislation of each participating country.

# Safety assessment

## Risks and benefit

This is an invasive and demanding intervention in a critical ill population and risk will apply. The project management has conducted an analysis of the benefit and risks of the study.

### Specific risk for interruption of ACLS quality

It is imperative that a new intervention should not interact negatively on the performance of the resuscitation. The REBOA procedure must therefore not influence negatively on the quality of the ACLS, all patients must receive standard pre-hospital care. The procedure may interrupt the ACLS because focus is drawn from the resuscitation to the REBOA procedure performed.

A structured educational program has been designed and formally evaluated ^48^ and all physicians that will include patients will be tested and certified before they can perform any clinical REBOA procedure. This ensure that all participants receive a standardized level of education and training, regardless of study site.

The risk of interruption of ACLS quality is most importantly mitigated through the structured educational program, regularly ACLS and REBOA training, simulation exercises and information to the emergency services at each study site. The pilot study demonstrates that REBOA is feasible in the pre-hospital setting, and that the intervention did not influence the quality of the ACLS ^1^. In the pilot study a three-step safety program was conducted.

In this trial, a similar safety program will also be conducted:

- After each randomised patient, the performing physician will be interviewed by the SI, following a semi-structured interview (appendix 29.6). Any safety concerns from the performing physician will be addressed.
- The ultrasound images obtained from patients in the intervention group will be reviewed by the SI and members of the project management or steering committee to ensure arterial placement of the guidewire.
- A case review of each randomised patient using all available information by an external expert panel consisting of an interventional radiologist, an intensivist and a pre-hospital physician. Hands-off time and duration of CPR effort will be specifically assessed.

### Specific risk of venous placement of REBOA catheter

One other anticipated risk is erroneous venous placement of the REBOA catheter. The femoral artery lies adjacent to the femoral vein. Femoral vein cannulation and subsequent occlusion of the vena cava inferior result in reduction of cardiac preload and must be avoided. Ultrasound guided cannulation is therefore mandatory. It is also mandatory to have two visible vessels before cannulation. With only one visible femoral vessel, it is impossible to establish if the vessel is a vein or artery. Out-of-plane cannulation technique is also mandatory, as this provides view of two vessels simultaneously. An in-line cannulation technique will not ensure arterial cannulation.

Any eventual venous cannulation can easily be used as a central venous line. If the balloon catheter is erroneously inflated in the vena cava inferior, we expect a rapid decrease in EtCO2.

The Norwegian national P-EMS include anaesthesiologists ^51^. These physicians will regularly be part of the resuscitation team at OHCA and provides a pre-hospital competency in establishing central vascular lines ^52^. Foreign study sites may involve physicians from other specialities than anaesthesiology, e.g. emergency physicians. However, all physicians involved in this study is familiar and competent in the Seldinger technique. Femoral access is preferable during CPR because resuscitation efforts limit access to the upper thorax and neck. Direct visualization of the femoral vessels with ultrasound facilitates catheterization during CPR ^53^. A blind, landmark-oriented approach to femoral catheterization is difficult in patients with low blood pressure or no palpable femoral pulse ^54^ and risks a higher rate of complications because femoral pulse is not located in 40% of CPR patients ^53^. A review-article reports that ultrasound guidance for femoral artery catheterization was associated with 49% reduction in overall complications, including hematoma and accidental venous puncture. It was also associated with 42% improvement in the likelihood of first-attempt success ^55^. Ultrasound is therefore considered mandatory in arterial cannulation during CPR.

### Other risks

This study adds a new treatment to patients with critical illness, in a setting where informed consent by the patient is impossible. It is imperative that no patients are subject to greater risks than the ones already related to the critical illness. Insertion of similar intravascular catheters are already in use for other indications, e.g. invasive arterial blood pressure measurements, and will in this study be performed by physicians well experienced in establishing vascular access in critical ill patients. The patients are at risk for local complications such as bleeding at the femoral site, but these complications, shared by other interventional procedures such as percutaneous coronary intervention (PCI), are not expected to represent serious adverse events.

Risk of lower limb ischemia

The REBOA technique is not new. The equipment is well used, in a range of indications and patient ages. Previously reported complications were after procedures where large gauge equipment was used, 10 to 14 French ^49,56^. It has been reported that these large sheaths may be associated with severe complications, including lower extremity ischemia and amputations ^57^. These complications may be related to the near-occlusive diameter of these larger sheaths, the length of time they remain in the artery, the location of insertion, and potential damage that can be caused during insertion. Studies show that smaller sheaths, 7Fr, are both safe and effective. These sheaths can remain in place for a prolonged time after insertion without severe complications ^58,59^. One study showed no vascular complications using 7Fr sheaths ^60^. A Norwegian study show that short introducer length (11 cm) was strongly associated with complications (local thrombus formation in the iliac or femoral artery) ^61^. One episode is reported of a tear of the aorta wall due to oversized balloon ^59^. The descending aorta is approximately 25 mm in width in the age span of the patient eligible for inclusion ^62,63^. The balloon catheter will reach no more than 10-20 cm outside the semi-rigid introducer, and both introducer and catheter will be fixated after insertion. Migration of the catheter with a theoretically potential damage to the aorta is therefore not likely. To minimize the risk of complications such as aortic rupture or local complications, a 7Fr introducer with a 20 mm balloon will be used.

Risk of organ ischemia

Aortic occlusion will limit blood flow to organs distal to the occlusion. One study advocated the use of repetitive deflations of the balloon every 10-15 minutes to minimize the risk of ischemic complications ^61^. We will not apply this regime, due to the low output state and marginal cardiac output generated with external chest compressions. The occlusion time will be limited, as clinical decisions for other resuscitation procedures, whether to stay on scene or continue CPR during transport to hospital, or when to terminate CPR efforts, is performed as in routine care, regardless of treatment with REBOA or not. One patient in the pilot study experienced ischemic colon and a hemicolectomy was performed ^1^. The incident was reported to the proper health investigational authorities. The following investigation concluded that the REBOA procedure was not the cause for this ischemic colon.

Risk of occlusion of carotid artery

The left subclavian artery springs from the aorta distal to the left carotid artery. A pulse check in left radial artery is performed before and after occlusion. If radial pulse is present after occlusion of the aorta, it is not likely that the balloon occludes carotid circulation.

Risk of increased bleeding proximal to balloon occlusion

One case report describe an intracranial haemorrhage in a multi-trauma patient receiving REBOA in the emergency department ^64^. REBOA could worsen bleedings proximal to the occlusion and we will not include patients where a neurologic injury (e.g. cerebral haemorrhage) is believed to be the aetiology of the cardiac arrest.

Risk of infection

The physicians are skilled in pre-hospital invasive techniques done under sterile condition (e.g. central vein punctures, pleura drainage catheters), and the risk of severe blood infection due to the procedure is considered low.

Risk to study personnel

The physicians are skilled in using equipment such as scalpel and needles. They will all participate in an educational program to ensure a safe and efficient REBOA technique. On each study site, training phantoms for REBOA technique training will be installed. This facilitates regularly team training on the procedure. Risk for mechanical injuries on the P-EMS crew or unnecessary injuries on the patient is considered low. If any needle puncture injuries should occur on the personnel, the procedure for such events at the local hospital will be followed.

### Autopsy

As in all pre-hospital managements of cardiac arrest, it is likely that several patients will be pronounced dead on scene or after ACLS efforts, regardless of REBOA placement. An autopsy could potentially provide information both on cause of death or complications of the ACLS or REBOA procedure. In Norway, autopsies are regulated in the “Autopsy Act” ^65^. This act separates “forensic autopsy” and “medical autopsy”. A forensic autopsy might be indicated if the body is of unknown identification or suspected criminal behaviour prior to the cardiac arrest. The decision to perform a forensic autopsy is made by the local police. Most pre-hospital deaths will not fall into this category. A medical autopsy is indicated for scientific reasons or for research. However, information to and consent from the next of kind is needed to perform a medical autopsy. It is not likely possible for the P-EMS crew to assess this information and consent in the pre-hospital setting. Also, it might not be ethically justified to use a pre-hospital emergency resource (ambulance or P-EMS crew) to transport the deceased to a university hospital to perform an autopsy.

However, this is a novel use of an invasive intervention and any information of potential harm caused by the REBOA equipment may be of interest. We will therefore try to obtain the next-of-kin’s consent to perform medical autopsy on patients that are admitted to hospital in Norway, but do not survive to hospital discharge.

### Steps to be taken to control or mitigate risks

- The physicians are all experienced clinicians, familiar and competent in Seldinger technique. All the personnel must participate in a structured training program and be certified before they can perform the procedure.
- The equipment is well known and used in a range of indications and patient ages.
- The equipment is small gauge, which limit the risk of local complications.
- Training facilities is available at all study sites.
- All emergency services, first responder services and physician manned local out-of-hours emergency facilities will receive extensive information of the procedure.

## Summary of risk assessment

These interventions have always been associated with risk. Lower gauge of equipment provides reduced frequency of risk. All equipment will be handled by experienced personnel and always according to current CE/FDA regulations, hence the equipment is approved for use in the patient cohort.

We argue that this research study is justified, based on the rationale described in the background section and in this chapter.

# Adverse events

The investigator is responsible for the detection and documentation of events meeting the criteria and definition of an adverse event (AE) or serious adverse event (SAE).

Please note that in the present trial all included participants are expected to meet one or more criteria for serious adverse events. The nature of the patient population studied, the prehospital environment, severity of illness included, and multitude of medical interventions makes the AE reporting challenging. Several events that meet the AE criteria are expected in the natural course of critical illness and the treatment offered to these patients.

Each adverse event (AE) will be assessed for seriousness, causality, severity and expectedness.

| **Seriousness** | As defined in the protocol |
| --- | --- |
| **Causality** | Not related |
|  | Unlikely |
|  | Possible |
|  | Probable |
|  | Causal relationship |
| **Severity** | Mild |
|  | Moderate |
|  | Severe |
|  | Life-threatening |
|  | Fatal |
| **Expectedness** | Expected event in ACLS or REBOA intervention |
|  | Unexpected adverse event |

## Definitions of adverse events and device deficiencies

The definitions in this chapter is based on those from *ISO 14155:2011 Clinical investigation of medical devices for human subjects — Good clinical practice*.

**Adverse event (AE)**

Any untoward medical occurrence, unintended disease or injury, or untoward clinical signs (including abnormal laboratory findings) in subjects, users or other persons, whether or not related to the investigational medical device (Figure 7).

Note 1: This definition includes events related to the investigational medical device or the comparator.

Note 2: This definition includes events related to the procedures involved.

Note 3: For users or other persons, this definition is restricted to events related to investigational medical devices.

**Serious adverse event (SAE)**

An adverse event that

a) led to death,

b) led to serious deterioration in the health of the subject, that either resulted in

1) a life-threatening illness or injury, or

2) a permanent impairment of a body structure or a body function, or

3) in-patient or prolonged hospitalization, or

4) medical or surgical intervention to prevent life-threatening illness or injury or permanent impairment to a body structure or a body function,

c) led to foetal distress, foetal death or a congenital abnormality or birth defect

Note 1: Planned hospitalization for a pre-existing condition, without serious deterioration in health, is not considered a serious adverse event.

**Adverse device effect (ADE)**

An adverse event related to the use of an investigational medical device

Note 1: This definition includes adverse events resulting from insufficient or inadequate instructions for use, deployment, implantation, installation, or operation, or any malfunction of the investigational medical device.

Note 2: This definition includes any event resulting from use error or from intentional misuse of the investigational medical device.

**Serious adverse device effect (SADE)**

An adverse device effect that has resulted in any of the consequences characteristic of a serious adverse event

**Unanticipated serious adverse device effect (USADE)**

A serious adverse device effect which by its nature, incidence, severity or outcome has not been identified in the current version of the risk analysis report

Note 1: Anticipated serious adverse device effect (ASADE) is an effect which by its nature, incidence, severity or outcome has been identified in the risk analysis report.

[figure not shown]

*Figure 7. Adverse events*

## Adverse events in the REBOARREST trial

Death is the most common outcome after cardiac arrest. Hence, we do not report death as a serious adverse event but register it as an expected outcome in the CRF.

All patients that achieve sustained ROSC will be transported to hospital and most will receive normal post-ROSC treatment, which include prolonged hospitalization and need of advanced medical and/or surgical interventions. It is therefore expected that nearly all subjects that achieve sustained ROSC will experience a serious adverse event after the definitions in this trial.

These SAEs are pre-specified outcomes and will not be reported but will be registered. We will therefore only report unexpected SAEs and SADEs/USADEs (events suspected related to the REBOA catheter and the handling of this equipment) to the sponsor and appropriate medicinal authority.

Adverse events will be documented in the CRF by the site investigator after the interview with the performing physician. If the patient is admitted to hospital, the SI will review the patient journal for documentation of adverse events 30 days after randomisation or if the patients dies prior to this. Adverse events that occur after this time will not be reported.

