## Exploratory endpoints

1. All-cause mortality one year after randomization
2. Difference in organ function, using the Acute Kidney Injury Network (AKIN) classification, liver function blood tests and others.
3. Incidence of all adverse events

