## Period for recording adverse events

For each patient the standard period for collecting and recording AE will be from randomization and until admission to hospital.

For each patient the standard period for collecting and recording SAE will be from allocation and until the 30 day follow up visit. At the 30 day visit an assessment will be made where we specifically ask for all SAEs prespecified in this protocol. We will also assess discharge notes for other events that fulfil the SAE definition and that can be assessed by the study team.

For patients still admitted to hospitals at day 30, an effort will be made to secure access to main discharge note for assessment for any SAE that has occurred between day 30 and discharge.

Any information that comes to investigators attention for any included patient prior to the end of trial will be assessed according to this protocol.

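### Section 14.2 bars reporting of adverse events after day 30, while 14.7 and 14.9 require later information to be assessed and suspected device effects reported; 14.2 and 14.7 also end AE recording at different points

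*Protocol*

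**What the plan says.** Protocol section 14.2 (Adverse events in the REBOARREST trial) says that for admitted patients "the SI will review the patient journal for documentation of adverse events 30 days after randomisation or if the patients dies prior to this". The next sentence is "Adverse events that occur after this time will not be reported". Nothing exempts events suspected to be caused by the catheter or its handling.

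Section 14.7 (Period for recording adverse events) gives two standard periods. For AEs, "the standard period for collecting and recording AE will be from randomization and until admission to hospital". For SAEs, "the standard period for collecting and recording SAE will be from allocation and until the 30 day follow up visit". It then goes beyond day 30 in two ways. For patients still admitted at that point, "an effort will be made to secure access to main discharge note for assessment for any SAE that has occurred between day 30 and discharge". For everyone, "Any information that comes to investigators attention for any included patient prior to the end of trial will be assessed according to this protocol".

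Section 14.8 (Recording of adverse events) has events between the end of pre-hospital treatment and day 30 collected from the discharge note and a paper form. Section 14.9.1 asks anyone who suspects an SAE, SADE or USADE to report it within 72 hours. Section 14.9.2 makes SADE/USADE reportable to the authority within 2 or 7 calendar days of sponsor awareness, depending on severity. Neither part of 14.9 sets a last day.

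Section 6.5 lists "Incidence of all adverse events" as an exploratory endpoint and gives no window. Section 10.3 says that adverse reactions over the 30-day period will be reported, and that each patient's trial period is one year.

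**The concern.** The sentence in 14.2 is an unqualified stop, whereas the sections on recording periods and on reporting do not stop there. A site that learns on day 40 of a suspected SADE would find three instructions: do not report (14.2), assess (14.7) and report to the authority (14.9.2).

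This matters because the procedure is invasive and new in this population. Section 11.2 says only that procedure-related effects are likely to be found within 30 days. Section 14.6 lists access complications such as pseudo-aneurysm, arteriovenous fistula and arterial stenosis, and the protocol nowhere says that these must appear within 30 days.

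The AE mismatch is a separate matter. An endpoint that covers all adverse events cannot be reproduced if one section stops recording non-serious events at the hospital door and two others continue to day 30.

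**Working it through.** No figure in the plan bears on this point, so the check is a comparison of texts, followed by a scale illustration.

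**1. The windows side by side**

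| Section | Events | Patients | Last day |
| --- | --- | --- | --- |
| 14.2 | Adverse events, no seriousness limit | Admitted patients | Day 30 or earlier death; later events not reported |
| 14.7, AE period | AEs | Each patient | Hospital admission |
| 14.7, SAE period | SAEs | Each patient | 30-day visit |
| 14.7, extension | SAEs, best effort | Still admitted at day 30 | Discharge |
| 14.7, last sentence | Any information, passively received | Any included patient | End of trial |
| 14.8 | Events after pre-hospital care | Each patient | Day 30 |
| 14.9 | SAE/SADE/USADE to the investigator; SADE/USADE to the authority | Any | None stated |
| 10.3 | Adverse reactions | Each patient | 30-day period |
| 6.5 | All adverse events | Not stated | Not stated |

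**2. Can the meaning of the word reported remove the conflict?** Section 14.2 distinguishes registering an event in the CRF from reporting it onward.
- If the last sentence of 14.2 concerns onward reporting, it bars after day 30 what 14.9 requires without a time limit.
- If it concerns recording, it contradicts the collection and assessment after day 30 in 14.7.

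A conflict remains on either reading.

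**3. Length of the affected period.** Follow-up is one year per patient (10.3). If the end of trial in 14.7 is read as at least that year, the stretch under conflicting rules is 365 − 30 = 335 days, about 11 months, for a patient who survives the year.

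**4. Non-serious events.** Section 14.7 ends AE recording at admission. Section 14.2 starts its journal review from admission and runs it to day 30, and 14.8 also collects to day 30. A non-serious event on hospital day 5 is outside the first rule and inside the other two.

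**5. Illustration of what pooling later events would do.** The protocol does not say that events after day 30 enter the incidence. The following shows the scale if they did.
- ROSC per 100 randomised, from the design rates in 9.2: 18 control, 36 REBOA.
- Share of ROSC patients still admitted at day 30: 5% to 30% (assumption; the documents give none).
- Patients covered by the discharge extension = ROSC × share. Control: 18 × 0.05 = 0.9 to 18 × 0.30 = 5.4. REBOA: 36 × 0.05 = 1.8 to 36 × 0.30 = 10.8.
- Share of those with a late SAE: 10% to 50% (assumption). Control: 0.9 × 0.10 = 0.09 to 5.4 × 0.50 = 2.7. REBOA: 1.8 × 0.10 = 0.18 to 10.8 × 0.50 = 5.4 patients per 100.

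The ratio of two between the arms is simply the ratio of the design ROSC rates (36/18), because the same shares are assumed in both arms. It is not evidence of harm.

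**The case against.** **A late device effect would be reported anyway.** Section 14.9 is mandatory, and the commitment in 14.2 to report SADE/USADE has no day limit of its own. The cut-off sentence follows text on the CRF and the journal review, so a careful site would not read it alone. This makes a lost report less likely, but the sentence is unqualified and a reader is entitled to take it literally. The claim is therefore that a report could be lost, not that the protocol as a whole permits it.

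**Expectedness is a separate filter.** Many vascular complications are listed as expected in 14.6, and expected serious events are restricted from reporting at any time. That stands. The conflict concerns events that would otherwise be reportable.

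**Two stronger readings are tempting.**
- A reader might infer that 14.7 goes beyond day 30 only for inpatients, so that late harm in discharged patients is ignored. That holds for active collection only. The last sentence of 14.7 covers any included patient whose information reaches an investigator.
- A reader might infer that SAE incidence is counted over a period that depends on survival and length of stay. The documents do not say so. Section 14.7 sets a standard SAE period to the 30-day visit for each patient, 10.3 reports the 30-day period, and no text puts later events into a between-arm count. The objective is descriptive, and details may lie in the SAP, which is not at hand. Section 14.2 also expects nearly all patients with sustained ROSC to meet the SAE definition, so pooling would change event counts more than the proportion of patients with an SAE.

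**Conclusion.** The contradiction is real. Section 14.2 ends reporting at day 30 without exception, 14.7 and 14.9 continue beyond it, and neither meaning of reporting reconciles them. Read literally, 14.2 could leave a late suspected SADE/USADE unreported during up to 335 days of a survivor's follow-up. Sections 14.2 and 14.8 also disagree with 14.7 on when recording of non-serious AEs ends.

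The number of events at stake cannot be derived from the documents; the range of 0.09 to 2.7 against 0.18 to 5.4 patients per 100 rests wholly on assumed shares and applies only if later events were pooled. Unequal observation is thus a risk to guard against, because active collection after day 30 depends on still being in hospital and 6.5 names no window. It is not a bias that the plan commits to. The primary endpoint and the sample size are unaffected. The point is worth an amendment because it concerns safety reporting and costs little.

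**What to change.** 1. Replace the last sentence of 14.2 with: *Adverse events after day 30 are not collected systematically; any suspected SADE/USADE that becomes known before the end of trial is recorded and reported under 14.9.* The expectedness rules in 14.2 and 14.6 are not altered by this.
2. State one AE recording window, in the same words, in 14.2, 14.7 and 14.8, and say whether it differs for serious and non-serious events.
3. In 6.5, or in the SAP if it does not already do so, state that the incidence endpoint uses the 30-day window already given in 10.3 and, for SAEs, in 14.7. List events between day 30 and discharge, and any learned of later, separately and outside the comparison between arms. Observation still ends at death within that window, so the endpoint remains descriptive, but the rule is the same in both arms.

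The cost is a few sentences in an amendment. Discharge notes are already to be obtained under 14.7 and 14.8, so nothing new is collected after day 30. If the single AE window is set to day 30, sites must abstract non-serious hospital events that 14.7 now omits; if it is set to admission, the endpoint in 6.5 should say that non-serious events are counted only to that point. The small downside is that late events appear in a listing and not in the comparative table.
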